## 6.1 Study Medication Description

Study medication for this trial will be maintained in bulk supply format, the vials will not be individually numbered. For both Curosurf® and BLES®, the correct dose, which is weight based, will be calculated by the study Investigator and the RT will be responsible to double check the calculation. Either study drug is given by endotracheal method within 48 hours of life. Repeated doses may be given, up to a maximum of 3. If further doses are required then open label BLES® should be administered. The doses should not be given more frequently than every 6 hours.

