# Study Medication/Intervention

Infants will be randomized in a 1:1 manner, to receive either the study drug, Curosurf® or the control drug, BLES®. The treatment dose for Curosurf® is 2.5 ml/kg (200mg/kg) for the first dose and 1.25 ml/kg (100mg/kg) for repeat doses. For BLES® the recommended dose is 5 ml/kg. Either drug is given by syringe into the endotracheal tube by a Respiratory Therapist. The SOP for administering both study drugs is found in Appendix E of this protocol.

After consent is obtained, and all inclusion/exclusion criteria are fulfilled an infant can be randomized into the trial. A blinded study RT will administer the drug according to the SOP found in Appendix E (also in the Resource Manual). The RT will document the procedure using the source documents provided by the sponsor and will also complete all Drug Accountability logs, as appropriate. Detailed instructions for completion of drug accountability logs are found in the Resource Manual.

The blinding procedure for administration of both study drugs is as follows:

- As the volume and viscosity of Curosurf® and BLES® are different, blinding of the RT administering the surfactant is not feasible. However, at any given time, two RTs work in the NICU. Doses of surfactant will be prepared away from the bedside by a RT not otherwise involved in the care of the infant. The surfactant will be drawn into a syringe and placed in a covered box. The RT will administer the surfactant with the syringe masked by a large label covering the amount of the contents. The RT will record in the patient’s chart that surfactant was provided but will not include the name or the dose of the product. This RT will not care directly for the infant for at least 48 hours following administration of the surfactant. The clinical and research teams will be blinded to the identity of the assigned surfactant throughout the study, unless an emergency occurs requiring unblinding

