# Appendix B: Extubation Criteria

Infants enrolled in the study will be extubated when they meet all of the following criteria:

1. rate on ventilator ≤40 per minute and
2. mean airway pressure ≤ 10 cm H20 and
3. fi02 ≤ 30%

Individual physicians can extubate patients from higher settings, at their discretion.

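### Section 6.1 has the Investigator calculate an arm-specific dose, which on its natural reading contradicts the promised blinding of the clinical and research teams

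*Protocol*

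**What the plan says.** **Who calculates.** Section 6.1, covering both products: "the correct dose, which is weight based, will be calculated by the study Investigator". The RT is to check the result.

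**What is calculated.** Section 6: "The treatment dose for Curosurf® is 2.5 ml/kg (200mg/kg) for the first dose and 1.25 ml/kg (100mg/kg) for repeat doses". For the control: "For BLES® the recommended dose is 5 ml/kg".

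**Who is meant to be blinded.** Section 6: "The clinical and research teams will be blinded to the identity of the assigned surfactant throughout the study", emergencies excepted. The same section has the drug drawn up away from the bedside by an RT with no other part in the infant's care, hides the syringe contents behind a label, and keeps product name and dose out of the chart. Section 7.2 has the allocation envelope opened by an RT who is not caring for the infant.

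**The administering RT.** Section 6 first says: "A blinded study RT will administer the drug according to the SOP found in Appendix E". Its blinding procedure then says: "blinding of the RT administering the surfactant is not feasible".

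**The endpoint.** Section 4.2 makes the primary endpoint alive and extubated at 48 hours. Section 4.1 has the RT and the physician assess readiness. Appendix B lists three numerical criteria and adds: "Individual physicians can extubate patients from higher settings, at their discretion".

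**The concern.** The blinding procedure in Section 6 treats the dose as information that would reveal the arm: the volume is masked on the syringe and left out of the chart. Section 6.1 then gives the Investigator the task of producing that same figure. Following both sections as written does not appear possible.

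This matters because the primary outcome depends in part on when a physician chooses to extubate, with stated room to act before the numerical criteria are met. Section 1.1 also records an expectation that Curosurf brings a rapid, marked improvement. A physician who shared that expectation and knew the arm could extubate Curosurf infants sooner than comparable BLES infants. Adjusting for centre and gestational age, as Section 8.2 plans, would not remove such a bias.

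**Working it through.** **Step 1. Does the volume identify the arm?** Inputs are the Section 6 volumes; let *w* be weight in kg, which Section 7.2 takes from the medical history.

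| | Curosurf | BLES | Ratio BLES : Curosurf |
|---|---|---|---|
| First dose | 2.5*w* ml | 5*w* ml | 5 / 2.5 = 2.0 |
| Repeat dose | 1.25*w* ml | 5*w* ml (assumed; no separate repeat volume is given) | 5 / 1.25 = 4.0 |

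The two volumes differ at every weight. Anyone who knows the weight and the assigned volume knows the product.

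**Step 2. Who is kept apart from care?**

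| Role | Access to the arm | Separation from the infant's care |
|---|---|---|
| RT who opens the envelope (7.2) | Yes | Stated: not involved in care |
| RT who prepares the dose (6) | Yes | Stated: no other part in care |
| RT who gives the dose (6) | Yes, by the blinding procedure; no, by the earlier sentence | Stated: no direct care for at least 48 hours (reading the sentence as referring to this RT) |
| Investigator who calculates the dose (6.1) | Yes, on the natural reading | None stated |

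**Step 3. Can the Investigator be involved in care?** Section 9.5 has the Investigator treat infants withdrawn for a serious adverse event, and Section 7.3.1 has the Investigator judge the need for surfactant beyond 72 hours. The role is therefore clinical. Neither section shows that the Investigator who calculates the dose is the physician who decides on extubation before 48 hours, and nothing in the protocol prevents it.

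**Step 4. Scale.** The plan's own figures come first. Section 8.1 gives 44 per group and 5% type I error. With a two-sided test and the normal approximation,

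z = [ |p2 − p1|·√n − 1.96·√(2p̄(1 − p̄)) ] / √[ p1(1 − p1) + p2(1 − p2) ], power = Φ(z).

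For p1 = 0.40, p2 = 0.693, n = 44, power is 79.9%. The other three rows of the table give 79.9%, 80.1% and 79.9%. A 30-point difference gives 81.9%, 83.1%, 85.2% and 88.0% at control rates of 40%, 45%, 50% and 55%. The stated power is reproduced, and the blinding point does not alter it.

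One infant's outcome moved across the 48-hour line changes the risk difference by 1/44 = 2.3 points. Against the table's detectable differences of 27.3 to 29.3 points that is about 8% (2.3/29.3 to 2.3/27.3). This is simply the granularity of an arm of 44. It does not estimate how many infants would be moved.

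**Step 5. Illustration under an assumed shift.** The documents give no figure for the effect of knowing the arm, so the shifts below are assumptions. There is no true treatment effect; knowledge of the arm raises extubation in one arm only. Rejection rates are exact, for the two-sided pooled z-test with 44 per arm.

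| Assumed shift | About how many of 44 | Rejection, control rate 40% | Rejection, control rate 55% |
|---|---|---|---|
| 0 points | 0 | 5.2% | 4.7% |
| 5 points | 2 | 7.5% | 7.5% |
| 10 points | 4 | 14.9% | 16.4% |
| 15 points | 7 | 27.6% | 31.9% |

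A small shift does little harm to the error rate; a moderate one does a good deal. Which of these applies cannot be read from the protocol.

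**The case against.** The strongest reply is that Section 6.1 opens by naming both products. It can be read as the Investigator working out a volume for each product from the infant's weight, which needs no knowledge of allocation. Sections 6 and 7.2 support this: only an uninvolved RT opens the envelope, and no step hands the result to the Investigator. This stands as a possible reading, so a reader who infers that the protocol definitely plans to unblind the Investigator goes further than the text. It is not the natural reading, because the sentence speaks of one correct dose, and nothing says the calculation comes before allocation is known. If it was the intent, it needs to be written down.

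Other stronger inferences are also unsupported:

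- *The Investigator decides the primary outcome.* Extubation is assessed by the RT and the physician. Overlap is possible but not stated.
- *The Investigator is re-exposed at every dose.* Section 6.1 does not say that the task covers each dose, though it discusses repeats in the same paragraph.
- *The Investigator's judgement on repeat doses affects the 48-hour endpoint.* Section 7.3.1 concerns the period beyond 72 hours. Section 7.2 sets the earlier conditions and names no decision-maker.
- *The endpoint is wholly discretionary.* Infants who meet all three criteria are to be extubated; the stated discretion runs only towards earlier extubation.
- *The trial could not be called blinded.* It claims only to be partially double-blinded, and a leak to one role would leave other staff masked. That label does not resolve the conflict, however: the only person the text says cannot be blinded is the administering RT.

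Operational detail may also sit in Appendix E, which is empty in the available text, or in the Resource Manual, which is not available. Even if so, Sections 6 and 6.1 would still disagree.

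**Conclusion.** The point holds as a contradiction that must be reconciled. On its natural reading, Section 6.1 reveals the arm to the Investigator, while Section 6 promises that the clinical and research teams do not know it. The wording on the administering RT is a second contradiction within Section 6 and needs no inference; its consequence is limited if the 48-hour separation from care applies to that RT.

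The risk to the primary endpoint is conditional. It requires that the Investigator learns the arm, that the same person takes part in extubation decisions, and that the knowledge changes those decisions. The protocol leaves the first two open and cannot inform the third, so the size of any bias is unknown. The correction is still worth making before recruitment, because bias that enters through extubation decisions cannot be repaired in the analysis.

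**What to change.** 1. **Section 6.1.** State that, before the envelope is opened, the Investigator confirms the weight and signs a form listing the protocol volumes for both products, first and repeat doses. After opening the envelope, the RT not involved in care selects and checks the assigned line. The completed form is kept from the clinical and research teams.
2. **Section 6.** Delete the word blinded where the administering RT is first described, and make clear to which RT the 48-hour separation from care applies.
3. **Accountability logs.** State that any log showing the product is kept from the blinded teams.
4. **Appendix E and the Resource Manual.** Bring them into line with the above.

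The cost is revised wording in the protocol and manual, and one pre-printed form. No extra staff are needed, no dose is altered, and the sample size stays at 44 per group.

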## 7.2 Baseline time point and Randomization

The baseline time point will occur after the consent has been obtained and the infant’s status fulfills the inclusion criteria, and no exclusion criteria. The following procedures will occur:

- Physical exam (includes vital signs) (the infant will not be reweighed for study purposes, the weight will be taken from the medical history)
- Medical History
- Concomitant medication history

The infant can then be randomized into the study. Each infant will be allocated to receive either Curosurf® (study drug) or BLES® (control) in a 1:1 ratio using a computerized random-number generator. Twins or higher multiples will be randomized as individual patients. Randomization will be stratified by center and by GA category (24-26 weeks and 27-31 weeks), with random block lengths. Allocation will be concealed in sealed, opaque, sequentially-numbered envelopes, which will be opened by a Respiratory Therapist (RT) not involved in the care of the infant. This will occur only after intubation. The drug will be prepared by the RT. Blinding procedures will occur as per Section 6 of this protocol.

A maximum of 3 doses can be given over a 72 hour period post randomization. Infants not extubated and requiring ≥30% oxygen with radiological evidence of RDS can receive further dose(s) of surfactant. Similarly, infants who fail extubation and need to be reintubated (criteria in Appendix C) could receive further dose(s) of surfactant if they require ≥30% oxygen with ongoing radiological evidence of RDS. The same blinding method will be used for each dose of surfactant given and each dose of surfactant will follow the randomization sequence (i.e. once randomized, an infant will receive the type of surfactant that was given at randomization).

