**7.3.1 Reintubation and further drug administration**

If an infant has failed extubation and requires reintubation, this information will be captured at the subsequent study timepoint. Further doses of surfactant can be given, if the maximum (3 doses) has not been already administered, up to a maximum of **72 hours** post randomization.

If the study Investigator deems that a subject needs further doses of surfactant beyond 72 hours post-randomization then this subject will be removed from the study and followed as per section 9.4 of this protocol.

## Week 2, Week 4 and Week 8

At weeks 2, 4 and 8 (if the infant has not been discharged) any information pertaining to SAEs (if within the 30 day follow-up for SAEs) and any extubation assessment data should be captured. If any infant that has been transferred to another institution the site must make every effort to follow the infant. This should be done in accordance with the local Ethics Boards guidelines and approval should be requested as necessary.

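### Sections 6.1, 7.2 and 7.3.1 conflict on surfactant beyond the dose maximum within 72 hours of randomization, and such a dose can fall before the 48-hour endpoint

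*Protocol*

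**What the plan says.** Four places in the protocol bear on this.

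- Section 6 (Study Medication/Intervention) gives the Curosurf dose as "2.5 ml/kg (200mg/kg) for the first dose and 1.25 ml/kg (100mg/kg) for repeat doses". Here a repeat dose is something other than the first dose.
- Section 6.1 says "Repeated doses may be given, up to a maximum of 3. If further doses are required then open label BLES® should be administered". This applies to both arms. The same section sets the spacing: "The doses should not be given more frequently than every 6 hours".
- Section 7.2 says "A maximum of 3 doses can be given over a 72 hour period post randomization". On masking it says "The same blinding method will be used for each dose of surfactant given". On product it says "each dose of surfactant will follow the randomization sequence", and explains that "once randomized, an infant will receive the type of surfactant that was given at randomization". It does not mention open-label BLES.
- Section 7.3.1 permits further doses "if the maximum (3 doses) has not been already administered", within 72 hours of randomization. An infant who needs surfactant after 72 hours leaves the study and is followed under section 9.4. The section is silent on product and on open-label BLES.

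The primary endpoint is being alive and extubated 48 hours after surfactant. The number of surfactant doses is a secondary outcome in Appendix D.

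**The concern.** A site with an infant who still needs surfactant after three doses, inside 72 hours, finds no single instruction. Section 6.1 points to open-label BLES or, on its other reading, to one more masked study dose. Section 7.2 puts a fourth dose over the cap and keeps every dose masked and on the assigned product. Section 7.3.1 does not allow the dose.

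Three things are at stake. The first is which product an infant in the Curosurf arm receives, because open-label BLES is the comparator. The second is whether the dose-by-dose masking in 7.2 still applies, which concerns both arms. The third is the ceiling on the number of doses, which could differ between centres that follow different sections. All three can arise before the primary endpoint is assessed.

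**Working it through.** The plan gives no figure for doses beyond the maximum, so there is none to reproduce. The check sets the sections side by side and then works out the timing.

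**Inputs.** Minimum interval between doses: 6 h (section 6.1). Dosing window: 72 h from randomization (7.2 and 7.3.1). Endpoint: 48 h after surfactant (Primary Endpoint). The protocol does not say which dose starts the 48-hour clock; the first dose is assumed here.

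**Step 1: the number of study doses.**
- 6.1, maximum includes the first dose: 3.
- 6.1, maximum counts only repeats, following the first/repeat distinction in section 6: 1 + 3 = 4.
- 7.2 and 7.3.1: 3.

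**Step 2: a fourth dose within 72 h.**

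| Text followed | Curosurf arm | BLES arm |
| --- | --- | --- |
| 6.1, 3 in total | open-label BLES | open-label BLES |
| 6.1, 3 repeats | masked Curosurf | masked BLES |
| 7.2 | over the cap; any dose given is masked Curosurf | over the cap; any dose given is masked BLES |
| 7.3.1 | not allowed; product not addressed | not allowed; product not addressed |

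**Step 3: does either reading of 6.1 remove the conflict?**
- *3 in total.* The count agrees with 7.2 and 7.3.1. The open-label dose still contradicts 7.2 on product in the Curosurf arm and on masking in both arms. It is also a dose that 7.3.1 does not permit.
- *3 repeats.* The fourth dose agrees with 7.2 on product and masking, but its existence contradicts the cap in 7.2 and 7.3.1. The product and masking conflict then moves to the fifth dose.

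Neither reading lets a site comply with all three sections.

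**Step 4: timing.** The earliest time of dose k after the first is 6 × (k − 1) h.
- Dose 4: 6 × 3 = 18 h, which is 48 − 18 = 30 h before the endpoint.
- Dose 5: 6 × 4 = 24 h, which is 48 − 24 = 24 h before the endpoint.

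Open-label BLES can therefore start at 18 h on the first reading and at 24 h on the second. Both times are arithmetic minimums. Section 7.2 also requires at least 30% oxygen and radiological RDS before a further dose, so actual times may be later.

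**The case against.** The strongest defence is that the sections describe two stages. Three masked doses make up study treatment. Section 9.4 lists completing the protocol-defined treatment as a reason to stop study product while follow-up continues. Surfactant after that is ordinary care, and 6.1 only names its product. The same-product sentence in 7.2 follows directly on the rules for study doses and could be limited to them. This is a sensible reading and may be what was meant. It is not written down, however: 7.2 speaks of each surfactant dose given, 7.3.1 makes further doses conditional on the maximum not being reached, and neither refers to 6.1. The operational rule may be in the Appendix E procedure or the Resource Manual. Their content is not in the available copy, so actual variation between sites cannot be confirmed. Even so, the protocol sections would still disagree.

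A reader might infer four stronger claims that the documents do not support.

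- *That 7.3.1 also fixes the product.* It sets only the cap and the 72-hour limit. The same-product rule is in 7.2 alone.
- *That total exposure differs by a known amount*: 200 + 2 × 100 = 400 against 200 + 3 × 100 = 500 mg/kg of Curosurf, or 3 × 5 = 15 against 4 × 5 = 20 ml/kg of BLES. These contrasts depend on the 1 + 3 reading of an ambiguous sentence. At the protocol's 5 ml/kg, a BLES infant given three study doses and one open-label dose also reaches 20 ml/kg, so the BLES totals do not separate the readings.
- *That the arms are pulled together at 48 hours.* No frequency of fourth doses is given. Infants who reach one have already needed more surfactant after three doses of the assigned product, and nothing shows that a change of product would alter their 48-hour outcome. Any power loss would rest on an assumed crossover share and on giving these infants the average success rate of their arm.
- *That open-label dosing reveals the allocation.* Under 6.1 the open-label product is BLES in both arms, so the dose alone does not identify the assigned surfactant. What is shown is a conflict with the masking rule in 7.2.

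**Conclusion.** The inconsistency stands. For surfactant beyond the maximum within 72 hours, the three sections disagree on whether it may be given, which product it is and whether it is masked. Section 6.1 is also ambiguous between 3 and 4 study doses. The conflict survives the more charitable reading of 6.1 and does not depend on the four-dose count.

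What can be sized is the timing: 18 h at the earliest for a fourth dose and 24 h for a fifth, both ahead of the 48-hour assessment. This rests on the 6-hour minimum interval and on an endpoint clock that starts at the first dose. The effect on the primary comparison is possible but unknown, because the number of infants concerned is not given. The sample size calculation is not affected. Intention to treat, stated in section 8.2, already keeps these infants in their assigned arm. The number of doses can be counted under any rule; only its ceiling depends on the section followed.

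This is more than a clerical matter, because the instruction determines which product infants receive, how many doses, and whether they are masked, before the primary endpoint is assessed.

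**What to change.** Reconcile sections 6.1, 7.2 and 7.3.1 into one rule, worded the same way in each. It should state:

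1. whether the maximum includes the first dose;
2. what, if anything, may be given after the maximum within 72 hours, with which product and whether masked.

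The clinical content is for the sponsor and investigators to decide. If open-label BLES is kept, section 7.2 should name it as an explicit exception to both the same-product rule and the masking rule, and the report should give, by arm, the number of infants who received it before 48 hours. No new rule on analysis assignment is needed.

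The cost is a wording change in three sections, a matching check of the Appendix E procedure and the Resource Manual, and, if open-label BLES is kept, recording the product and time of those doses. No patients or procedures are added.

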**Adverse Reactions**

Both study drugs have potential adverse reactions and the study staff should carefully monitor the infant for any or all of the following:

**Adverse Reactions of both Curosurf**® **and BLES**®

- Bradycardia and hypotension -during administration

**Adverse Reactions of Curosurf**®

- patent ductus arteriosus
- intraventricular hemorrhage of all grades,
- pneumonia
- sepsis
- pulmonary interstitial emphysema,
- pulmonary hemorrhage
- pneumothorax
- recurrent apnea
- retinopathy of prematurity,
- bronchopulmonary dysplasia

**Adverse Reactions of BLES**®

*Very common adverse* events occurring in10% of infants who received BLES® (bovine lipid extract surfactant), in descending order of frequency, were:

- patent ductus arteriosus
- decreased post-dose pulmonary function values,
- intraventricular hemorrhage of all grades,
- sepsis,
- retinopathy of prematurity,
- bradycardia
- severe intraventricular hemorrhage

*Common adverse events* occurring in1% and < 10% of infants who received BLES®, in descending order of frequency, were;

- pulmonary interstitial emphysema,
- periventricular leukomalacia,
- pneumothorax,
- pulmonary hemorrhage,
- endotracheal tube complications,
- necrotizing enterocolitis,
- respiratory acidosis,
- convulsions,
- hypotension,
- apnea,
- hydrocephalus
- pneumonia

.

